### Criteria for success

This study will be considered appropriate to proceed to a full trial if:▸Patients and local collaborators report generally positive views about acceptability of randomisation and of intervention as determined by evaluation of feedback forms;▸A suitable sensitive outcome measure is determined and sample size estimated;▸Local collaborator intervention-fidelity rate is at least 80%.

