### Identification and recruitment of participants

Local collaborators will be asked to identify people referred to their service who are suitable for the pilot using the inclusion and exclusion criteria (Table 1) and invite them to participate. Local collaborators will complete a log to record the number of people with a diagnosis of PPA who do not meet the inclusion criteria, they will also record the number of people who are eligible but who have declined to participate in the study and their reasons why if provided. People who meet the inclusion criteria will not be under any obligation to take part in this research and this will be made clear from the outset. Potential participants will be provided with a participant information sheet (see Additional file 1) before informed consent is obtained at least 48 h later (see Fig. 2 for consent flowchart).

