### Assessment of acceptability of the intervention

In order to ensure the treatment is acceptable to people with PPA, their CPs and local collaborators, each will be asked to provide feedback on the intervention. Accessible feedback forms will be given to participants with PPA and their CPs at every intervention session, to be completed and returned anonymously in pre-stamped addressed envelopes directly to the first author. Additionally, local collaborators will be asked to include feedback on acceptability as part of the adherence questionnaire, completed after every session.

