### Data analysis

Analysis for this single blind, randomised controlled pilot study will involve both quantitative and qualitative methods. Language and quality of life assessment data will be entered into a database and analysed using the Statistical Package for the Social Sciences [33]. All data will be explored to test for assumptions of normalcy. If assumptions are not met, appropriate non-parametric tests will be used. Repeated measures ANOVA will be used in the analysis with group (no speech and language therapy treatment, BCPPA treatment) as a between subject factor and time (pre-therapy and post-therapy) as a within subject factor. This information will be used to determine a suitable sensitive outcome measure and to perform a power calculation to determine sample size for a fully powered trial. Conversation data will be analysed following a procedure developed for the BCA intervention [21] to identify change in the use of targeted strategies following intervention. This will involve counting barrier and facilitator behaviours in 5-min video samples selected from the pre- and post-intervention conversation samples. These counts will be analysed using Poisson Trend Test suitable for observations occurring in Poisson distribution. All pre-therapy conversations will be weighted the same as one another, as will all the post therapy conversations. Outcomes for different participants will be investigated using a Test for Homogeneity, where this is significant, and the effect for different dyads will be calculated using the Holm-Bonferroni procedure.

Descriptive statistics will be used to report recruitment, attendance, attrition, and reasons for dropout. A CONSORT (Consolidated Standards of Reporting Trials) and SPIRIT (Standard Protocol Items: Recommendations for Interventional Trials) [27] flow chart will be used to present overall recruitment to and progression through the study (Fig. 1). Recruitment and retention rates will be used to support sample size calculations to inform a future full trial and plan the required number of sites to meet this target. Adverse events will also be recorded, and participant feedback forms examined to inform future recruitment procedures. Stroke-related aphasia trials in the UK NHS have reported recruitment rates of between 38 and 44% from potential participants at the research sites [34–36].

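### The go criterion judges acceptability of randomisation from feedback forms alone and leaves out the logged refusals, so it leans towards acceptable by an amount that cannot be estimated

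*Protocol article*

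**What the plan says.** Acceptability of randomisation is the first item listed under Aim in the protocol article, and again in the Abstract. Under Criteria for success, the first of three conditions for a full trial is: "Patients and local collaborators report generally positive views about acceptability of randomisation and of intervention as determined by evaluation of feedback forms". The second is "A suitable sensitive outcome measure is determined and sample size estimated", and the third is a fidelity rate of at least 80%.

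The forms are described under Assessment of acceptability of the intervention. For couples: "Accessible feedback forms will be given to participants with PPA and their CPs at every intervention session". For therapists: "local collaborators will be asked to include feedback on acceptability as part of the adherence questionnaire, completed after every session".

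Refusals are recorded. Under Identification and recruitment of participants, sites keep a log in which they "record the number of people who are eligible but who have declined to participate in the study and their reasons why if provided". Under Data analysis, "Descriptive statistics will be used to report recruitment, attendance, attrition, and reasons for dropout", and "Recruitment and retention rates will be used to support sample size calculations to inform a future full trial". No condition under Criteria for success mentions the log, the consent rate or withdrawals.

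**The concern.** An eligible couple who refuse because therapy might be withheld are the most direct evidence that randomisation is not acceptable. The stated rule gives that couple no weight. Every couple whose form is read has already accepted randomisation by consenting, so their views are a selected sample for this question.

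Such refusals are foreseeable on the article's own account. The Background describes people with primary progressive aphasia as often strongly motivated to seek speech and language therapy, and the control arm goes without it for 5 weeks. The go condition could be met with favourable forms while an appreciable share of eligible couples had declined for this reason. The main trial would then start with its first feasibility question answered from the wrong people.

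**Working it through.** There is no stated figure to reproduce. The check traces which evidence reaches the decision.

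| Evidence | Who supplies it | Stated use | In the go criterion for randomisation? |
|---|---|---|---|
| Couple feedback forms | Couples attending intervention sessions | Acceptability | Yes |
| Collaborator questionnaire | Treating therapists, after sessions | Acceptability, adherence | Yes |
| Decline log with reasons | Eligible people who refuse | Recorded by sites | No |
| Recruitment and retention rates | All approached or enrolled | Sample size and number of sites | No |
| Attrition and reasons for dropout | Enrolled couples who leave | Descriptive report | No |

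**Coverage.** The target is 42 couples allocated 1:1, so 42/2 = 21 per arm. As described, forms reach at most 21 of 42 randomised couples (50%) and none of those who declined. Giving forms to the control arm as well would raise 21 to 42, but the number of decliners heard would stay at 0. Control-arm feedback is therefore a separate matter.

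**Direction.** Let C be the couples who consent, p the share of them with positive views, and R the eligible couples who decline because of randomisation or the no-therapy arm. A form-based reading estimates p. Counting the R couples as negative gives pC/(C + R). This cannot exceed p, and equals it only when R = 0 (or p = 0). Leaving R out can only favour acceptable.

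**Size.** The only recruitment benchmark in the article is 38 to 44% of potential participants in stroke-related aphasia trials. Applied to 42 couples:

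- 42/0.44 = 95.5 (96), so 96 − 42 = 54 not enrolled
- 42/0.38 = 110.5 (111), so 111 − 42 = 69 not enrolled

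These 54 to 69 people would include the ineligible as well as refusers, and the benchmark comes from another population. Nothing says what fraction would refuse because of randomisation, so R could lie anywhere from 0 up to these totals. That range is too wide to serve as an estimate. The criterion also has no numerical threshold, so no tipping point can be calculated.

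**The case against.** The strongest reply is that refusals are handled elsewhere. They are logged, recruitment is reported descriptively and in a flow chart, it is reviewed every 2 months (Sample size justification), and the rates are used to set the sample size and number of sites. A low uptake would be seen and planned for. This stands, and it limits the harm. It does not close the gap, because an overall recruitment rate does not separate objection to randomisation from other reasons for not taking part, and reporting a rate is not the same as letting it bear on the go decision.

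Second, local collaborators' views are part of the criterion, and they are the people who invite couples and hear the refusals. This also stands in part: a reader might infer that acceptability is judged only by people who agreed to be randomised, and that is not so. But the feedback described for collaborators sits in an adherence questionnaire completed after intervention sessions. It is at best an indirect route for refusers' reasons.

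Third, the descriptive list under Data analysis names reasons for dropout but not reasons for declining. In a condensed article, with the flow chart not available here, that is weak evidence that they will go unreported. I rest nothing on it beyond a small wording change.

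**Conclusion.** The point holds as a weakness in a stated decision rule: the rule names feedback forms as its evidence, and those forms cannot reach the people whose refusal bears most directly on the question. The bias is towards acceptable. This rests on two assumptions: that the forms are distributed as the article describes, and that at least some eligible couples decline because of randomisation. If none do, the rule gives the same answer either way.

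Two stronger readings are not supported. A reader might infer from the 38 to 44% benchmark that a large share of eligible couples will refuse randomisation. The benchmark does not measure refusals among eligible invited couples and gives no reasons. A reader might also infer that the study ignores refusals. It records them and uses recruitment for planning; what it does not do is bring them into the go criterion. This is a modest, inexpensive improvement and does not undermine the pilot.

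**What to change.** Split the first go condition so that randomisation and intervention are judged separately. For randomisation, consider the forms together with the decline log and report:

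- the number and proportion of eligible invited couples who declined;
- the number citing randomisation or the no-therapy arm, as a proportion of eligible invited couples, with a 95% interval;
- the number who declined without giving a reason;
- withdrawals after allocation is disclosed, by arm.

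Add reasons for declining to the descriptive list under Data analysis.

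Reasons are recorded only where offered, so the proportion citing randomisation is a lower bound. It should be shown beside the total decline rate and the number with no reason given. For the same cause I would not impose a fixed ceiling on it, since a site could pass simply because people did not explain themselves.

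The log and dropout data are already being collected. The cost is a simple rule for coding reasons and a small amendment to the go criterion. Recruitment began in November 2017, so the change should be dated and, if possible, made before the log is summarised.

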### Assessment and management of risk

This is a low-risk study. It is possible that participants will not experience improvements as a result of the intervention. However, there is evidence to suggest that such interventions are effective for improving communication and well-being in adults with non-progressive aphasia and their carers [14]. Importantly, there is no evidence to indicate that participants will experience any harmful effects. Most of the measures used in this study are frequently used in routine clinical practice with people with PPA. Additionally, the local collaborators are SLTs with skills to complete measures in a sensitive and supportive manner, minimising risk of distress. If participants do not feel emotionally or physically well enough to continue, then an assessment will be postponed. Video recording of conversations might also cause distress. To minimise the risk, we will ensure that as far as possible, the participants are familiarised with recording devices and understand why video recording is necessary. All procedures are set out within our participant information sheets (see Additional file 1) and consent forms, which were co-produced with the study steering group of people with PPA and their carers. Participants will be reminded that they can withdraw from the study at any time without giving a reason. Any adverse events will be recorded in the participant’s medical record, and the study sponsor informed.

## Discussion

To the best of our knowledge, this is the first randomised controlled UK pilot study of a conversation training intervention for people with PPA and their families. It will inform the feasibility of delivering a future full randomised controlled trial investigating the effectiveness of the BCPPA program in an NHS setting. There is little documented evidence of the impact of communication training for people with PPA and their CPs, yet there are reports of its widespread clinical use by SLTs across the UK [15, 16]. As in prior functional communication-focused PPA intervention studies [41], BCPPA might improve subjective confidence in communication (using the Communication Confidence Rating Scale in Aphasia [42] see Table 2 list of pre- and post- intervention measures) even if there is no clear impact on specific language measures, as well as potentially improving carer wellbeing. Thus, insights from this study will be of relevance to guide development of future research and in particular, trials of therapeutic interventions in PPA, as well as for clinical care for this population. The paucity of literature on functional communication-focused interventions for people with PPA makes the findings of interest to dementia researchers and SLTs, as well as people with PPA and their family members. The study will generate a unique dataset of language, conversation, and quality of life measures from people living with PPA and family members. It will lead to the identification of sensitive measures of the impact of functional communication-focused interventions for PPA. Additionally, the study will provide a rich source of information on acceptability of the BCPPA program to people with PPA and their CPs. Importantly, this study involves people with PPA and their families, and a group of expert SLTs, in the development of a manualised intervention program that meets their communication needs.

Study limitations include the inability to blind participants to group allocation, a common barrier in behavioural studies. Those allocated to the control group will not receive any intervention for 4 weeks as there is no comparable standard care intervention. Similarly, it is not possible to blind local collaborators delivering the intervention. For this reason, post-intervention assessment is not completed by the local collaborators but by pairs of junior researchers who will be blinded to group allocation. The inclusion criteria for this study may result in significant heterogeneity across participants in terms of language profile and communication difficulties, making it difficult to compare participants’ skills pre and post intervention. Thus, a range of outcome measures are being piloted across language, communication, and quality of life to identify the most sensitive across all participants. BCPPA is designed to be tailored to an individual’s needs, which may result in variation in the types of strategies identified and practiced. To counter this, the key components of BCPPA remain fixed, and measures of fidelity will demonstrate the consistency with which the intervention in delivered. A further potential limitation is ascertainment bias since access to speech and language therapy for PPA varies widely across the UK, and some of the likely barriers to access (socio-economic, cultural, linguistic, etc.) could also influence BCPPA outcomes. Despite these limitations, this study represents an important step toward a future full-scale RCT to determine the effectiveness of BCPPA for people with PPA and their family members.

The results of this study will be disseminated via presentations at national and international conferences and submitted for publication in peer reviewed scientific journals. In the medium term, the BCPPA program and training materials will be made available to SLTs via UCL’s public e-learning platform, alongside BCA [18]. With support from the study steering committee, results will be disseminated through professional and user group networks via publications and presentations, for example, at the PPA support group branch of the Rare Dementias Support Group based at UCL (http://www.raredementiasupport.org/).

### Trial status

Trial registration number ISRCTN10148247. Recruitment commenced in November 2017 and is due to end in March 2019.

## Abbreviations

BCA: Better Conversations with Aphasia
BCPPA: Better Conversations with Primary Progressive Aphasia
CP: Conversation partner
ISRCTN: Numerical identification of randomised controlled trials
MRC: Medical Research Council
NHS: National Health Service
PPA: Primary progressive aphasia
RCSLT: Royal College of Speech and Language Therapists
SLT: Speech and language therapist
UCL: University College London
